#### Phase III: Cost-effectiveness analyses

All relevant costs related to developing and implementing the intervention, minus the cost caused by the study, will be collected. This will include the cost of developing the SMS/VM platform as well as all the fixed and variable costs of running the intervention for one year. We will look at the cost of engaging and linking participants but will not include the cost of the health services that participants use as a result of the program. In that way, we are looking at the cost-effectiveness of adding the SMS/VM component to SRH services. We will use five measures of effect that will be self-reported by participants during baseline and follow-up surveys: uptake of first HIV test (0 to1); uptake of regular HIV test (at every six months for those engaging in unprotected sex with sweethearts or engaged in sex work); uptake of first visit to a SRH care provider for any testing services or counselling; uptake of any visits to a SRH care provider for any testing, services, or counselling; and uptake of condom use at last sex.

An average cost-effectiveness ratio (CER) will be calculated by dividing the total cost of each arm by the change in outcomes of each arm. In addition, the incremental CER (ICER) will be calculated, which will measure the cost per additional HIV test/visit/protected sex under the *Mobile Link* as compared to no SMS/VM intervention.

#### Control group

Participants in the control group will receive the current existing standard of care, but not the health-related SMS/VMs or associated follow-up phone calls. Standard of care consists of access to existing HIV and SRH services which includes: face-to-face counseling; free HIV and STI testing and condoms; and clinic phone numbers and hotline phone numbers with a toll-free help line for clients staffed by trained counselors. Control group members will receive “check-in” reminder calls before questionnaire appointments (midline and endpoint).

### Primary outcomes

All outcomes will be self-reported and collected through surveys. The primary outcome measures will include: (1) HIV testing; (2) condom use at last sex; (3) frequency of condom use (always, sometime, rarely, never) with clients; (4) frequency of condom use (always, sometime, rarely, never) with boyfriends; (5) STI screening when experiencing symptoms; (6) STI treatment when diagnosed; (7) contraceptive use; (8) unwanted pregnancy and unsafe abortion; and (9) experiences with GBV.

### Secondary outcomes

The secondary outcome measures will include: (1) knowledge of SRH; (2) knowledge and attitudes toward existing SRH resources; (3) knowledge and attitudes toward abortion laws and services; (4) knowledge and attitudes regarding risk within relationships; (5) attitudes toward condom use and condom negotiation; (6) experiences of STI symptoms; (7) received STI diagnosis; (8) self-reported HIV status; (9) utilization of peer counselor; and (10) utilization of any other SRH services.

### Data collection

Data collection tools will include baseline and follow-up questionnaires administered by a data collection team. The baseline questionnaire will contain questions to collect information on contact details; demographics; pathways to entertainment work; information about their current workplace; SRH knowledge, attitudes, and behaviors; sexual relationships; condom use self-efficacy; and experiences with GBV. All questions will be asked in both written and oral forms because literacy rates are not 100% in this community. In addition, all data collected via weekly monitoring surveys will be analyzed on a routine basis.

### Data management

Data coding, quality control, and data entry will be done following established procedures at KHANA. Pre-coded questionnaire will be used to minimize data coding errors. All data forms and questionnaires will be checked for errors by a second data collector; errors and necessary corrections will be made before data entry. A database will be developed for data entry in MS Access, which will include built-in range and within- and between-variable consistency checks. The program will also run error-checking applications and produce reports of inconsistencies to be checked daily.

### Analysis plan

#### Analyses of participant characteristics

Participant characteristics and survey responses will be analyzed using descriptive statistics including Chi-square test of homogeneity and paired Student’s *t*-tests to compare characteristics between the participants to ensure balance among the study arms.

#### Sensitivity and per-protocol analyses

We will conduct an additional sensitivity analysis including only participants who completed the six-month follow-up. Per-protocol analysis will be undertaken to assess the impact of the intervention among those who actively participated in the intervention. Participants who respond to > 50% of the six VM/SMS over the intervention period will be considered highly protocol-adherent. Participants who respond to 0.5–50% will be considered less protocol-adherent. Those who never responded to a voice message will be considered as never-responding and not included in the sensitivity analysis.

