### Participant selection criteria

All participants must: (1) work at an entertainment venue in the selected study sites; (2) be currently sexually active defined as having engaged in oral, vaginal, or anal sex in the past three months; (3) own a mobile phone; (4) know how to retrieve VM or retrieve and read SMS on a mobile phone (Khmer or Romanized Khmer); (5) self-identify as a FEW; (6) be willing to receive two SMS/VM per week for one year; (7) provide a written informed consent; and (8) agree to a follow-up visit after six months and 12 months. Figure 1 depicts participant flow diagram for the study.

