#### Phase II: Intervention

The *Mobile Link* intervention comprises a series of automated SMS/VMs to participants’ mobile phones over the 12-month period. Participants will receive the first message within the first day of the intervention. The messages will be designed to enhance and increase utilization of existing HIV and SRH services by reminding clients about safe sex methods available to them and providing a conduit for additional support. Upon enrollment into the study, participants in all groups will receive a face-to-face baseline behavioral survey conducted by a data collection team who remained masked to intervention allocation at enrollment.

The baseline questionnaire (see Additional file 5) was designed by the study team using sections from standard questionnaires currently in use at KHANA for assessing similar measures in populations of high-risk women in Cambodia. The questionnaire was created in English, translated to Khmer, and back-translated to English. The questionnaire will be pilot tested with 15 FEWs similar in eligibility to future study participants using cognitive interviewing techniques [48]. Next, participants will be randomized into intervention and control groups: Group 0 is the control group and Group 1.1 and 1.2 are the intervention group (1.1 = SMS [1.1a Khmer characters or 1.1b Romanized Khmer] or 1.2 = VM in Khmer).

Those in the control group will get one “check-in” SMS or VM between baseline and midline and another between midline and endline. Participants will be asked to confirm receipt of this message. These messages will contain no health information and will be used as a way to stay in touch with participants and to compare “receipt confirmation” rates to the intervention group. All participants will be asked to choose whether they would prefer to receive SMS or VM and their reason for their choice. If they choose SMS, they will be asked if they prefer Khmer characters or Romanized Khmer. Recent studies on choosing the method for receiving interventions during an RCT have demonstrated that it may increase participation and retention [49].

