A message schema was developed in which each participant will receive a message from a different topic group each week for 10 weeks. The messages will tend to follow a flow of rights-based health information and then linkage (though there is some variance depending on topic). However, after each message, participants will also have the option to be linked to an outreach worker. After the tenth week, the topic areas will cycle through again, but the messages within the topic areas will be unique. After weeks 30, 40, and 50 (+ 2), messages will be repeated to reinforce particular concepts and ideas. Participants who indicate they would like to talk to a counselor will receive a call from a *Mobile Link* staff. The counselor will provide individualized information via telephone or face-to-face on that particular topic and, if needed, can escort the participant to receive the required services.

Participants will also receive a weekly 5–7-question survey that asks about more common and/or time-sensitive issues such as STI symptoms, vaginal infection/irritation, support for GBV, or psychological issues. Once a month, participants will be asked if they are using contraception and/or want to be linked to family planning counseling. Participants who endorse any of the survey questions will be asked if they want to be linked to an outreach worker. Therefore, it is important to note that, while the topics in the messages will change each week—as well as the topical prompts for linkages to outreach workers—the weekly monitoring survey provides another consistent and constant platform for mobile linkage.

Trained data collectors and community health workers in the selected sites will deliver the *Mobile Link* intervention. SMS/VM are scheduled and sent using the open-source software program developed by InSTEDD (instedd.org). InSTEDD and the Project Coordinator will retain data on the SMS/VM messages sent, responses to messages, and outcomes of follow-up phone calls.

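### Per-protocol adherence is graded on six messages, but the article describes weekly messages for a year and no set of six; the never-responder rule covers voice messages only

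*Protocol article*

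**What the plan says.** Under Sensitivity and per-protocol analyses, the protocol article sets the aim: "Per-protocol analysis will be undertaken to assess the impact of the intervention among those who actively participated in the intervention". Three response groups follow.

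- High: "Participants who respond to > 50% of the six VM/SMS over the intervention period will be considered highly protocol-adherent".
- Lower: "Participants who respond to 0.5–50% will be considered less protocol-adherent".
- None: "Those who never responded to a voice message will be considered as never-responding and not included in the sensitivity analysis".

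The programme is described under Phase II: Intervention. It "comprises a series of automated SMS/VMs to participants’ mobile phones over the 12-month period", and "each participant will receive a message from a different topic group each week for 10 weeks". The topics then cycle again with new messages, and the schedule is carried through weeks 30, 40 and 50 (+ 2). A weekly survey of 5–7 questions runs alongside. Participants choose text or voice messages.

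Participant selection criteria require each woman to "be willing to receive two SMS/VM per week for one year". The Discussion again refers to weekly messages.

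**The concern.** The adherence rule and the intervention description do not fit together. The rule refers to six messages over the intervention period as if they were a known set, but nothing else in the article defines or mentions one. The only other small count is the two check-in messages sent to the control group, which is neither six nor part of the intervention.

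The never-responder group has a separate fault. It is defined by voice messages only, although text messages are an equal option. A woman who chose text messages receives no voice messages, so she can never have answered one, and the literal rule excludes her however often she replied.

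At stake is who counts as an active participant. The analyst cannot apply the rule without repairing it, and different repairs put the same woman in different groups. If the repair is chosen after outcomes are known, the per-protocol result is open to selection.

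**Working it through.** **Inputs from the article**

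- Stated denominator: 6 messages; high means more than 50% (Sensitivity and per-protocol analyses).
- Intervention period: 12 months, taken as 52 weeks (Phase II: Intervention).
- Topic messages: 1 a week; surveys: 1 a week (Phase II: Intervention).
- Messages accepted at enrolment: 2 a week for one year (Participant selection criteria).

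**Step 1. Can six be reproduced?** Number of messages = messages per week × weeks.

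| Reading | Calculation | Messages | Replies needed for more than 50% |
|---|---|---|---|
| As stated | – | 6 | 4 |
| Topic messages, six months only | 1 × 26 | 26 | 14 |
| Topic messages, one year | 1 × 52 | 52 | 27 |
| Two a week, or topic message plus survey, one year | 2 × 52 | 104 | 53 |

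None of these readings gives six. Six messages are 6/52 = 11.5% of the yearly topic messages, or 6/104 = 5.8% of two a week.

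**Step 2. What if six were a subset?** The article names no subset, so this is an assumption made only to gauge size. Take six messages chosen at random and independent replies with probability p.

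- On six: P(high) = P(X ≥ 4), X ~ Bin(6, p).
- On 52: P(high) = P(X ≥ 27), X ~ Bin(52, p).

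| Reply rate p | High on six | High on 52 |
|---|---|---|
| 0.40 | 0.18 | 0.05 |
| 0.50 | 0.34 | 0.45 |
| 0.60 | 0.54 | 0.91 |
| 0.70 | 0.74 | 1.00 |

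For p = 0.60 on six: 15 × 0.1296 × 0.16 + 6 × 0.07776 × 0.4 + 0.046656 = 0.311 + 0.187 + 0.047 = 0.54.

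**Step 3. Without the independence assumption.** Fix a woman's yearly total and draw six of her 52 messages at random (hypergeometric). With 31 of 52 answered (59.6%) she belongs in the high group, but at least 4 of the six are answered with probability only 0.54. With 21 of 52 answered (40.4%) she does not belong there, yet is graded high with probability 0.17. The result is close to Step 2.

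**Step 4. The never-responder rule.** No arithmetic is needed. Text and voice are alternative modes, and the rule names voice only. Read literally, all women who chose text messages fall in the excluded group.

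**The case against.** The strongest case on the other side is that this is one wrong number in a supplementary analysis. The primary outcomes are analysed by intention to treat, and effectiveness is judged on the group-by-time interaction, not on adherence groups. A designated six would make the groups a coarse proxy rather than meaningless, and a condensed article cannot prove that no such set exists elsewhere. The voice-only wording may also be loose drafting, since the sentence on high adherence names both modes. All of this limits the consequence. It does not supply the six or make the rule workable as printed.

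A reader might also infer more than the article supports:

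- **That four replies in a whole year make a woman highly adherent.** This takes the threshold from six messages and the replies from 52. The rule states a share of six. At reply rates of 5%, 10% and 15%, P(at least 4 of 6) is 0.0001, 0.0013 and 0.006, and the chance of passing half of 52 is practically zero. Both rules agree there; they part in the middle range.
- **That a woman who reads everything but needs no help is a non-responder.** The article does say that "after each message, participants will also have the option to be linked to an outreach worker". But Phase II also plans to compare receipt-confirmation rates between the control and intervention groups, and Additional analyses lists message responses and linkages separately. A response is therefore not the same as a linkage request.
- **That the 0.5% lower bound distorts the groups.** It is an odd figure, but for any denominator below 1/0.005 = 200 it classifies exactly as any reply at all does.
- **That the eligibility criteria and the schedule contradict each other.** One topic message plus one survey is two contacts a week, so they can agree. The article does not say that this is meant.

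**Conclusion.** The point holds. The stated denominator of six disagrees with the article's own schedule on every reading tried, and the voice-only definition of never-responders does not fit a programme in which women choose text or voice. As written, the rule cannot correctly identify active participants.

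The size is moderate. Under the assumed random six, a woman who answers 60% has a 0.54 chance of being graded high, against 0.91 on 52 messages; for one who answers 40% it is 0.18 against 0.05. These figures rest on a random subset and independent replies, neither of which the article states. Step 3 shows that the independence assumption matters little.

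Only the per-protocol and sensitivity analyses are touched. The article gives no ground for saying that the intention-to-treat result is affected or that the groups could carry no information at all. The correction should be made, but the primary conclusion does not depend on it.

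**What to change.** In Sensitivity and per-protocol analyses:

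1. Delete the reference to six messages.
2. Define adherence as the share of topic messages actually sent to the woman in her chosen mode, counted from the platform log up to the survey being analysed, that she answered or confirmed.
3. Use three bands (more than 50%, above 0 to 50%, and none) and apply all three to text and voice alike.
4. State whether the two messages a week in the eligibility criteria count the weekly survey, so that the denominator is the same throughout.

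The cost is a wording change. Phase II: Intervention already provides for keeping records of messages sent and responses received. Trial status says recruitment has not started, so the rule can be settled before any data exist.

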**Methods:**

A two-arm RCT will be used to determine the effectiveness of a mobile-phone-based text/voice messaging intervention. The intervention will be developed through a participatory process. Focus group discussions and in-depth interviews have been conducted to inform and tailor behavior change theory-based text and voice messages. During the implementation phase, 600 FEWs will be recruited and randomly assigned into one of the two arms: (1) a control group and (2) a mobile phone message group (either text messages [SMS] or voice messages [VM], a delivery method chosen by participants). Participants in the control group will also receive a weekly monitoring survey, which will provide real-time information to implementing partners to streamline outreach efforts and be able to quickly identify geographic trends. The primary outcome measures will include self-reported HIV and sexually transmitted infections (STI) testing and treatment, condom use, contraceptive use, and gender-based violence (GBV).

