#### Additional analyses

We will provide a descriptive analysis of information on study-related mobile phone use among participants. The aim will be to include number of voice message and phone interactions, response to voice messages, response to weekly surveys, time spent on phone calls, and linkages to outreach workers to facilitate description of process indicators and any issues. Additionally, at the end of the trial, the costs of the intervention (training, human resources, phone costs, and so on) will be estimated.

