## Discussion

Finding better strategies for linking hard-to-reach populations who are at risk for HIV to quality health services is a global health priority. The World Health Organization (WHO) has stated that a worldwide failure to provide adequate HIV services for key populations such as men who have sex with men, people in prison, people who inject drugs, sex workers, and transgender people may be a barrier to achieving progress toward reversing the HIV epidemic [50]. Previous studies have highlighted the unique challenges to linking key populations to HIV services in Asia [32, 33, 37].

In Cambodia, the 2008 “brothel ban” and consequent surge in indirect sex work has created additional barriers to connecting vulnerable and high-risk FEWs with health services. The *Mobile Link* trial aims to link FEWs to services and increase risk-reducing behaviors using a technology women use daily to connect with family and friends [42, 44, 51]. Weekly messages tailored to their specific needs may improve their knowledge and attitudes toward connecting with services and promote positive behavior change.

We anticipate several limitations associated with recruitment, retention, and measurement in this study. Our study population is a hidden, hard-to-reach group that is mobile, at least across entertainment venues. As such, we anticipate challenges in recruiting and following-up with participants over the 12-month study period. We will make efforts to address these limitations by providing incentives for participation, making frequent contact through mobile phones, collecting phone numbers from all currently owned SIM cards at baseline and midline, and asking for the contact information for their next nearest contact.

Another concern is the broad range of literacy rates within our study population which may affect the quality of participation and length of retention. In our feasibility studies, we tested small groups of FEWs for reading and writing literacy [35]. Most women received the highest literacy rating but several received the lowest rating. In addition, KHANA staff have reported that they have encountered problems with reading comprehension within this population. For this reason, the VM option within the intervention arm of the study was added. Recent evidence suggests that offering a choice of participation mode within an RCT can improve both recruitment and retention [50].

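### The never-responding rule counts voice messages only, contradicting the VM/SMS adherence tiers beside it and, read literally, excluding women who chose SMS from a sensitivity analysis first defined as all six-month completers

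*Protocol article*

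**What the plan says.** Delivery mode is one or the other, at the participant's choice. The abstract describes the intervention as "either text messages [SMS] or voice messages [VM], a delivery method chosen by participants". The Phase II section says "All participants will be asked to choose whether they would prefer to receive SMS or VM and their reason for their choice" and codes the intervention subgroups separately: "1.1 = SMS [1.1a Khmer characters or 1.1b Romanized Khmer] or 1.2 = VM in Khmer".

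The section on sensitivity and per-protocol analyses does four things in one paragraph:

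- It defines the sensitivity analysis as restricted to women who completed the six-month follow-up.
- It introduces a per-protocol analysis among women who took an active part in the intervention.
- It sets two adherence tiers. The upper one is explicit about both modes: "Participants who respond to > 50% of the six VM/SMS over the intervention period will be considered highly protocol-adherent". The lower one is "Participants who respond to 0.5–50% will be considered less protocol-adherent".
- It closes with an exclusion: "Those who never responded to a voice message will be considered as never-responding and not included in the sensitivity analysis".

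**The concern.** The closing sentence names voice messages only, in a trial where a woman may receive SMS instead. Read as written, it has two consequences.

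First, a woman on SMS cannot meet the condition for staying in, because she is sent no intervention voice message to answer. Her engagement plays no part in the decision. The intervention women left in the analysis would be those who chose VM and answered at least once, so the set is selected by delivery mode as well as by response.

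Second, the sentence applies a message-response criterion to the sensitivity analysis, which the paragraph has already defined by follow-up completion. A response criterion belongs with the per-protocol analysis. As the text stands, it is unclear which of the two analyses loses these women.

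At stake is the make-up of a supporting analysis set. If the conflict is left open, someone must choose between the two readings later, possibly after seeing data.

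**Working it through.** The article gives no figure to reproduce. The check is a classification exercise followed by simple counting.

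**Step 1: classes on the stated base of six messages.** One response is 1/6 = 16.7%, three are 3/6 = 50% and four are 4/6 = 66.7%. The lower tier (0.5% to 50%) is therefore 1 to 3 responses, and the upper tier (above 50%) is 4 to 6.

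**Step 2: apply both rules to a woman who chose SMS.**

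| SMS answered | Tier (counts VM/SMS) | Literal never-responding rule (counts VM) |
|---|---|---|
| 0 of 6 | none | never-responding, excluded |
| 1 to 3 of 6 | less adherent | never-responding, excluded |
| 4 to 6 of 6 | highly adherent | never-responding, excluded |

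In the last two rows she falls into two classes that should be mutually exclusive. For a woman who chose VM, the two rules agree.

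**Step 3: count the intervention women affected.** The arm size is 300 (Study design). Let s be the share choosing SMS. The article gives no value, so s = 30% to 70% is an assumption.

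- s = 0.30: 300 × 0.30 = 90 women
- s = 0.50: 300 × 0.50 = 150 women
- s = 0.70: 300 × 0.70 = 210 women

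These are counts before attrition of women excluded whatever they answered. Those who answered no SMS would be never-responding under a corrected rule as well, so the number wrongly excluded is smaller by that group.

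**Step 4: can a loss of precision be stated?** Only by adding an assumption about controls. The exclusion sentence names no arm, and Phase II has controls choosing a mode too and confirming receipt of check-in messages. Ignoring attrition, venue allocation and non-response among VM users:

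- Controls all kept: the standard-error ratio is √[(1/n₁ + 1/300)/(2/300)]. This is 1.10 with n₁ = 300 − 90 = 210, and 1.47 with n₁ = 300 − 210 = 90.
- SMS-choosing controls dropped too, with the same s in both arms: the ratio is 1/√(1 − s), which is 1.20 at s = 0.30 and 1.83 at s = 0.70.

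The answer changes with the reading, so no single inflation follows from the text.

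**Step 5: test the correction.** If never-responding means no response to any message in the chosen mode, the classes become 0, 1 to 3 and 4 to 6 of six. They do not overlap, they cover everyone, and mode no longer decides inclusion.

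**The case against.** The strongest reply is that this is a slip of wording in a supporting analysis. The tier sentence counts both modes, so an analyst would very likely read the last sentence the same way, and the primary analysis is by intention to treat. Both points stand. They limit the importance of the matter but do not remove it: the exclusion is stated outright, and nothing in the text says which sentence governs.

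Four stronger readings are tempting, and the article does not support them:

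- **That all SMS users will in fact be dropped.** This takes one side of a contradiction as settled. It is the literal result, but probably not the intended one.
- **That the standard error rises by 10% to 47%.** This needs the assumed SMS share and an intact control arm of 300. An analysis of completers would not have that arm, and the text does not say that controls are exempt.
- **That the remaining women would be a lower-literacy group.** The Discussion, having described reading problems, says "For this reason, the VM option within the intervention arm of the study was added". That explains why the option exists, not who takes it up. Choice is by preference, and the same section reports that most women tested received the top literacy rating. A literacy difference is possible, no more.
- **That the process evaluation will leave out SMS.** The Additional analyses section says "The aim will be to include number of voice message and phone interactions, response to voice messages, response to weekly surveys". This is a loosely worded descriptive list. Its survey-response and outreach-linkage items are not tied to voice, and Phase II commits to keeping data on SMS and VM sent and answered.

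It is also fair to say that correcting the voice-only wording leaves the tiers resting on six messages, which sits awkwardly with a messaging programme lasting a year. That is a separate question.

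**Conclusion.** The point holds as an internal contradiction in a stated exclusion rule. The tiers count VM and SMS, the never-responding class counts VM only, and the exclusion is applied to an analysis that the same paragraph defines by six-month completion. Read literally, the rule removes intervention women who chose SMS regardless of engagement and leaves a set selected by delivery mode.

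The size is conditional: 90 to 210 of 300 intervention women before attrition if 30% to 70% choose SMS, a share the article does not report. No single figure for lost precision can be given, because the treatment of controls is unclear. The intention-to-treat primary analysis is unaffected. The matter is worth correcting because the rule as written would build the wrong analysis set and the correction is simple.

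**What to change.** Redefine never-responding as no response to any message in the participant's chosen mode, SMS or VM. Apply that class to the per-protocol analysis only, and keep the sensitivity analysis as all women who completed the six-month follow-up. Optionally, reword the Additional analyses section so that messages and responses are described for both modes.

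The cost is a few wording changes. No new data are needed, because the article already plans to retain SMS and VM sending and response records.
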